### Feasibility

Twelve hospitals, both university medical centres and community hospitals, will participate in this trial. The study group consists of hernia experts from these 12 centres, who frequently perform laparoscopic as well as open hernia surgery. These hospitals perform about 20-30 incisional hernia corrections a year, and aim for an inclusion of 10-15 patients each year.

We aim for 125 patients per year, hence 12-13 inclusions every month. This is highly feasible, because these 12 centres together perform over 300 incisional hernia repairs annually. We aim for participation of more centres along the way, but only experienced laparoscopic surgeons can participate.

### Time schedule

Study preparation and formation of a core study group is already in progress. Initiation of the INCH-trial around 1-8-2012 after METC permission is obtained in each hospital. We aim for an inclusion rate of 10-15 patients per month. About 28 months are needed to include the amount of patients needed to calculate the difference in length of hospital stay. After this period the trial will continue; to meet the secondary end-point a longer follow-up period is needed. The follow-up will be continued at 3 and 5 year after index surgery. Patients who don’t want to participate and patient who are excluded will be registered.

### Ethical approval and safety monitoring

According to the ‘Good Clinical Practice’ rules, ethical approval has been asked and obtained from the Medical Ethical Board (METC) of the VU University Medical Center. This is an independent board and they will supervise the trail and make decisions about all possible changes in the study through amendments. The board will also monitor the possible complications.

No experimental surgery is performed; all the surgical techniques used are already part of our daily practice. All hospitals record (post-operative) morbidity according to guidelines of the Dutch Society of Surgeons. Adverse effects will be registered and told to the METC.

#### SAE’s

All individual Serious Adverse Events (SAE’s) will be registered and reported to the CCMO. Sepsis and possible re-operation due to a missed bowel perforation after laparoscopic incisional hernia repair, as well as death in the direct post-operative phase will be reported within 7 days. Permission has been obtained for ‘line listing’ for all other individual SAE’s; the METC permits to report all other events once every 6 months.

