**Figure 2 F2:**
[figure not shown]
Classification of incisional hernias according tot the European Hernia Society.

Postoperatively: open or laparoscopic/length of the scar/duration of surgery/type of mesh used/size of the mesh/type of mesh fixation/presence of bleeding/accidental bowel lesion/use of tubes/use of per-operative antibiotics/possible re-operation.

Inpatient: daily VAS score/use of analgesics/length of hospital stay/morbidity/mortality/QOL at two days post-surgery.

During Follow-up at 2 weeks and 3 months: healthcare and lost productivity costs/QOL at 2 weeks and 3 months post-surgery will be measured through the Short Form 36 and the Carolina Comfort Scale/time to return to work/recurrence/pain/wound infection/patient satisfaction/other morbidity.

During long-term follow-up at 1, 3 and 5 years: Recurrence/pain/wound infection/patient satisfaction/other morbidity.

**Primary outcomes** are:

Length of hospital stay. This is the time until discharge. A patient can be discharged when he/she is able to move normally, tolerate a normal diet and has a VAS painscore < 5 without the use of opiates.

Quality of life measures through SF-36 and CCS.

**Secondary endpoints** are:

Re-operation rate for recurrence or complications of the incisional hernia repair. The analysis will be continued after the cost-effectiveness study has ended, a longer follow-up is needed to examine the recurrence-rate.

28 days post surgery morbidity and mortality,

Total mean costs will be related to the following effect measures in the cost-effectiveness analyses:

1) Time to full recovery.

2) Quality-adjusted life-years (QALYs) based on the SF-36D
[11].

Intention to treat analysis will be performed. Blinding is impossible as the surgical difference is visible from the outside.

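### Seven-day reporting of re-operation for a missed bowel perforation is written for laparoscopic repair only, so the same event after open repair can fall to the six-monthly listing

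*Protocol article*

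**What the plan says.** The SAE's section of the protocol article sets two reporting speeds.

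- **Fast.** One sentence names three events: sepsis, "re-operation due to a missed bowel perforation after laparoscopic incisional hernia repair", and early post-operative death, the last in the words "as well as death in the direct post-operative phase will be reported within 7 days".
- **Slow.** For everything else a line listing has been agreed, and "the METC permits to report all other events once every 6 months".

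The same section says that all individual SAEs are registered and reported to the CCMO, without a time limit. It does not say who receives the 7-day reports.

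The section Ethical approval and safety monitoring gives the METC supervision of the trial and says of it: "The board will also monitor the possible complications". It adds "Adverse effects will be registered and told to the METC", again without a time limit.

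The Case record form section lists, for every operation and beside the item for open or laparoscopic approach, "presence of bleeding/accidental bowel lesion/use of tubes/use of per-operative antibiotics/possible re-operation". A secondary endpoint is "Re-operation rate for recurrence or complications of the incisional hernia repair", with no restriction to one technique.

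**The concern.** The fast-reporting rule ties one serious complication to one of the two techniques under comparison. Death, in the same sentence, carries no such tie, so the qualifier on perforation does limit something. The protocol foresees bowel injury and re-operation after either technique, since it records both for every patient and compares re-operation between the groups. It gives no reason for treating the reports differently.

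What is at stake is safety oversight. Treatment is unblinded, and the METC is the board said to monitor complications. Between two listings it could know of this event after laparoscopic repair and not yet of the same event after open repair. Harm in patients who had open repair could come to its notice late.

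**Working it through.** The protocol states no figure on this point that could be reproduced. The check is a reading of the rule, followed by a comparison of the two time limits.

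**Step 1. Apply the rule as written.** Take a patient re-operated for a missed bowel perforation and ask which timetable applies.

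| Accompanying event | Laparoscopic repair | Open repair | Converted repair |
|---|---|---|---|
| Early post-operative death | 7 days | 7 days | 7 days |
| Sepsis, no early death | 7 days | 7 days if sepsis is a separate item; otherwise six-monthly | 7 days if sepsis is a separate item; otherwise unclear |
| Neither | 7 days | Six-monthly | Unclear |

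The middle row depends on grammar. The words limiting the rule to laparoscopic repair follow both sepsis and the re-operation, and could govern the second alone or both. The text does not settle this. The bottom row holds on either reading.

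The converted column is unclear because the Treatment section allows a change to open surgery during a laparoscopic repair, while the reporting rule refers to the repair done and not to the arm assigned.

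**Step 2. Look for a sentence that closes the gap.** Two come close: SAEs are reported to the CCMO, and "Adverse effects will be registered and told to the METC". Neither gives a time limit, so neither brings the open-repair event onto the 7-day timetable.

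**Step 3. Compare the limits.**

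- Six months in days: 6 × 365.25 / 12 = 182.6, about 183 days.
- Ratio of the two limits: 182.6 / 7 = 26.1.
- If events fall evenly between listings (an assumption), the mean wait for a listing is 182.6 / 2 = 91.3 days, or 91.3 / 7 = 13.0 times the 7-day limit.

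**Step 4. Patients randomised within one listing interval.**

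- Feasibility section, 125 patients per year: 125 / 2 = 62.5, about 31 per arm with equal allocation.
- Time schedule section, 10 to 15 per month: 6 × 10 = 60 to 6 × 15 = 90, or 30 to 45 per arm.

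These are patients, not events. The article gives no rate of missed perforation after open repair, so the number of delayed reports cannot be derived from it.

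**Step 5. Check whether the trial's results are touched.** The case record form collects bowel lesion and re-operation for both procedures, and the endpoint definitions make no distinction. The reporting rule therefore changes neither the endpoint data nor the sample size.

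**The case against.** The strongest reply is that the restriction may be deliberate and accepted. The METC has agreed to the line listing, and a board that knows the terms also knows that no 7-day report is due for this event after open repair. The protocol scrutinises laparoscopy more closely elsewhere: the Background calls it potentially difficult, and the criteria for participating centres require a recording of a laparoscopic operation and guidelines for safe laparoscopy. Six-monthly reporting is also a permission, so nothing bars earlier reports. Finally, this is a condensed article, and the full protocol may spell out the procedure differently.

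Part of this stands. Agreement by the board makes it less likely to be misled, and the condensed source lowers confidence that practice is as asymmetric as the printed rule. But the article states a specific rule and gives no reason for its one-sidedness. That is more than detail left to a fuller document. If the event is rarer after open repair, symmetric reporting only becomes cheaper.

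A reader might infer more: that the board could not compare the arms fairly, or might act against laparoscopy on one-sided information. The document does not support this. Single-case expedited reports are alerts, the article describes no interim comparison or stopping rule that uses them, all SAEs are registered, and both groups are visible at each listing. Nor is the METC the only recipient of safety information, since SAEs also go to the CCMO.

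**Conclusion.** The point holds in a narrow form and is of minor severity. As printed, re-operation for a missed bowel perforation after open repair, without early death and (if sepsis is a separate item) without sepsis, may be reported up to about 183 days later, where the same event after laparoscopic repair is due within 7. If the laparoscopic qualifier also governs sepsis, the gap is wider. The status of converted cases is not determined.

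This rests on reading the sentence literally and on the full protocol not saying otherwise. The 26-fold ratio compares two maximum limits and is not an expected delay. It would go too far to call this a rule for the laparoscopic arm, because the wording follows the procedure, or to see in it a bias in the trial's results.

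**What to change.** Reword the sentence in the SAE's section so that the events already on the expedited list (sepsis, re-operation for a missed bowel perforation, early post-operative death) are reported on the same timetable for patients in both randomised arms, and say explicitly that converted repairs are included. Present the six-monthly line listing by randomised arm.

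The cost is one sentence, a notification to the METC and a small number of extra expedited reports. The change concerns reporting only; treatment, data collection, endpoints and sample size stay as they are.

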#### Criteria for participating centres

Participating surgeons have already performed at least 50 open and 50 laparoscopic incisional hernia repairs. They will hand over an unedited recording of a laparoscopic incisional hernia repair of their own. The principle investigators will review their recordings. Guidelines to perform a safe laparoscopic procedure will be made. Participating surgeons have to follow the guidelines.

### Goal

The goal of the trial is to establish whether laparoscopic incisional hernia repair is superior to conventional open incisional hernia repair in terms of cost-effectiveness. This is measured through length of hospital stay and quality of life. Secondary endpoints are re-operation-rate (due to complications or recurrence), morbidity, mortality and shape of the abdomen.

In current surgical practice there is on going discussion about the possible benefits of laparoscopic incisional hernia surgery. Scientific evidence is lacking to determine whether laparoscopic correction is superior to conventional open techniques in terms of cost-effectiveness.

## Discussion

The difference in time to full recovery between the two treatment strategies is thought to be in favor of laparoscopic incisional hernia repair. Laparoscopic incisional hernia repair is therefore expected to be a more cost-effective approach.
